### 2.4. Sample Size

The planned sample size for this trial is 63 women with breast cancer undergoing active oncological treatment, with 21 participants allocated to each of the three study arms: health education control group (G0), individual cognitive training group (G1), and ALMA group intervention (G2).

The sample size calculation was based on the primary outcome, defined as the change in objective global cognitive performance from baseline (T0) to post-intervention (T1), assessed using the Montreal Cognitive Assessment (MoCA). As no directly comparable previous trial evaluating the ALMA intervention in women with breast cancer was available, the expected effect was estimated using an indirect reference study that evaluated a multicomponent cognitive stimulation programme and reported a mean post-intervention increase of 2.95 points in MoCA score [27]. Assuming a common standard deviation of 3.48, this corresponded to an estimated standardized effect size of Cohen’s d ≈ 0.85.

For the purposes of sample size estimation, this effect was converted to an approximate ANOVA effect size of f ≈ 0.40. The calculation was performed using G*Power software, version 3.1.9.7 [28], for a balanced one-way fixed-effects ANOVA with three independent groups, an alpha level of 0.05, statistical power of 80%, and equal allocation across groups. Under these assumptions, a minimum total sample of 57 participants was required to detect an overall between-group difference.

To account for an anticipated attrition rate of approximately 10%, the recruitment target was increased to 63 participants, corresponding to 21 participants per study arm. This inflation is intended to preserve statistical power for the primary analysis under the intention-to-treat principle.

Although the primary effectiveness analysis will be conducted using linear mixed models to evaluate the Group × Time interaction across baseline and post-intervention assessments, the ANOVA-based sample size calculation was used as a conservative and transparent approximation for planning purposes. Linear mixed models are expected to make efficient use of repeated-measures data and to accommodate missing outcome data under the missing-at-random assumption. Therefore, the ANOVA-based calculation was considered appropriate for estimating the minimum feasible sample size while maintaining consistency with the planned three-arm randomized design.

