### 3.1. Outcome Definitions and Scoring Direction

All outcomes will be assessed at baseline (T0) and after the conclusion of the four-month intervention period (T1). For each outcome, change scores will be calculated as the post-intervention score minus the baseline score (T1 − T0). The direction of clinical interpretation depends on the scoring system of each instrument.

For the primary outcome, a positive change in the Montreal Cognitive Assessment (MoCA) total score will indicate improvement in objective global cognitive performance.

While the MoCA is a screening instrument, its designation as the primary endpoint is clinically justified by its widespread validation, brief administration time (minimizing evaluation fatigue in active cancer patients), and extensive use as a benchmark across CRCI trials, allowing for direct cross-study comparisons. Furthermore, the MoCA exhibits superior sensitivity to the specific neurocognitive phenotypes of “chemobrain” compared to other global screeners, as it incorporates rigorous subtests dedicated to executive functions, working memory, sustained attention, and delayed verbal recall. To actively mitigate the inherent risk of Type II errors and address potential ceiling effects in this relatively young and functional patient population, the MoCA is structurally supplemented within this multi-method protocol by robust secondary measures capable of capturing subtle cognitive fluctuations.

For FACT-Cog, higher scores indicate enhanced cognitive functioning and elevated cognitive-related quality of life. For the PECC and the Lawton and Brody Scale, higher scores are indicative of better every day cognitive performance and greater functional autonomy, respectively. Conversely, higher scores on the Hamilton Anxiety Scale, Pittsburgh Sleep Quality Index, ECOG Performance Status Scale, and Everyday Life Memory Failures Questionnaire will indicate worse anxiety symptoms, poorer sleep quality, poorer functional performance status, and more frequent everyday memory failures, respectively.

The primary endpoint will be the between-group difference in change in MoCA total score from T0 to T1. The primary comparison will be between the ALMA group intervention (G2) and the health education control group (G0). Secondary comparisons will include G2 versus G1. The G1 versus G0 comparison, if reported, will be interpreted as exploratory.

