### 3.9. Statistical Analysis

All analyses will be conducted according to the intention-to-treat (ITT) principle, including all randomized participants in the groups to which they were originally allocated, regardless of adherence to the intervention, thereby ensuring that the primary effectiveness analysis remains fully powered even if a significant proportion of participants fail to meet compliance thresholds. A secondary per-protocol analysis may be conducted including participants who complete the post-intervention assessment and, in the intervention arms, meet the predefined adherence criteria (≥70% attendance). In the event that a large majority of participants fail to reach this updated 70% attendance threshold due to severe treatment-related toxicity, a secondary sensitivity dose–response analysis will be implemented, modeling session attendance as a continuous covariate to evaluate the threshold-independent impact of intervention volume on neurocognitive outcomes.

Descriptive statistics will be used to summarize baseline sociodemographic and clinical characteristics by study arm. Continuous variables will be presented as means and standard deviations or medians and interquartile ranges, depending on their distribution. Categorical variables will be presented as frequencies and percentages. Baseline comparability between groups will be described, but statistical testing of baseline differences will not be used to determine participant inclusion or exclusion from the analysis.

The primary effectiveness analysis will evaluate change in Montreal Cognitive Assessment (MoCA) total score from baseline (T0) to post-intervention assessment (T1). Linear mixed models (LMM) will be constructed using a Restricted Maximum Likelihood (REML) estimation approach. The model will include fixed effects for group, time, and the Group × Time interaction term, and a parsimonious random-effects structure restricted to a random intercept for each participant to account for within-subject correlation across time while excluding random slopes. The Group × Time interaction will be the main parameter of interest. Both unadjusted and adjusted models will be calculated to verify the robustness of the intervention effect.

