The planned between-group comparisons for the primary outcome will focus on the ALMA group intervention (G2). The first planned comparison will evaluate the difference in change in MoCA total score from T0 to T1 between G2 and the health education control group (G0). The second planned comparison will evaluate the difference in change in MoCA total score from T0 to T1 between G2 and the individual cognitive training group (G1), in order to assess the potential added value of the multidimensional group-based ALMA intervention over individual cognitive training. The comparison between G1 and G0 will not be considered a planned efficacy comparison and, if reported, will be interpreted as exploratory.

To strictly prevent statistical overfitting and safeguard the degrees of freedom given the target sample size of 21 participants per study arm, the adjusted model will be parsimoniously restricted. Specifically, a maximum of two pre-specified baseline covariates will be simultaneously controlled for as fixed effects: chronological age (in years) and educational level (in years of formal schooling). Baseline cognitive stratification variables will be excluded from the model as covariates, given that their equilibrium across groups is already mathematically guaranteed by the stratified block randomization procedure (Section 2.5). Additional clinical and psychological variables including disease stage, treatment modality, time since diagnosis, cancer-related fatigue/performance status, baseline anxiety symptoms (Hamilton Anxiety Scale), and baseline ECOG Performance Status will be exclusively examined in exploratory or sensitivity analyses rather than included simultaneously in the primary adjusted model.

Because two planned comparisons will be conducted for the primary outcome, namely G2 versus G0 and G2 versus G1, Holm–Bonferroni correction will be applied to these two comparisons to control the family-wise error rate. Holm–Bonferroni correction will also be applied to secondary outcome comparisons within each outcome family when appropriate. Any additional post hoc analyses, including G1 versus G0 comparisons, will be clearly labelled as exploratory.

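### The trial is sized on a three-group omnibus ANOVA but decided on two Holm-adjusted contrasts with no stated power; on the plan's own inputs G2–G0 has about 63–73%, and 57 does not give 80% at the stated f = 0.40

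*Protocol article*

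**What the plan says.** Section 2.4 bases the calculation on the T0–T1 change in MoCA. The reference study "reported a mean post-intervention increase of 2.95 points in MoCA score". "Assuming a common standard deviation of 3.48", the plan obtains d ≈ 0.85, converts it to f ≈ 0.40, and runs G*Power "for a balanced one-way fixed-effects ANOVA with three independent groups, an alpha level of 0.05, statistical power of 80%, and equal allocation across groups". This gives 57 women to detect an overall between-group difference, raised to 63 (21 per arm) for about 10% attrition. Although the analysis will use a mixed model, "the ANOVA-based sample size calculation was used as a conservative and transparent approximation for planning purposes".

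Section 3.9 makes Group × Time the main parameter, names G2–G0 and G2–G1 as the planned comparisons, and states that "Holm–Bonferroni correction will be applied to these two comparisons to control the family-wise error rate". Tests are two-tailed, and primary significance is p < 0.05 after that correction. The same section describes the intention-to-treat analysis as "ensuring that the primary effectiveness analysis remains fully powered even if a significant proportion of participants fail to meet compliance thresholds".

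Section 1 ranks G2–G0 as the primary hypothesis and G2–G1 as the second. Section 3.1 names G2–G0 as the primary comparison and adds: "Secondary comparisons will include G2 versus G1".

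**The concern.** The test that was sized is not the test that decides the trial. A 2-df F test at 0.05 asks whether any arm differs. The primary result depends on two single contrasts, the smaller p-value of which must fall below 0.025. A reader of Section 2.4 will take the trial to have 80% power for ALMA against health education, and the document gives no figure to support that.

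Two further statements add to this impression. One calls the calculation conservative. The other says that intention-to-treat keeps full power under poor adherence. In addition, the sections rank G2–G1 differently, so the alpha that applies to G2–G0 and the meaning of a result positive for G2–G1 alone are not settled.

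**Working it through.** **Inputs.** Section 2.4: effect 2.95, SD 3.48, f ≈ 0.40, alpha 0.05, power 80%, N = 57 (19 per arm), recruited 63 (21 per arm). Section 3.9: two-sided contrasts, Holm, so 0.025 at the first step and 0.05 at the second. d = 2.95/3.48 = 0.848.

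**1. The plan's own figure.** Omnibus power comes from the noncentral F with df (2, N − 3) and noncentrality N·f².
- f = 0.40, N = 57: 57 × 0.16 = 9.12, power 75.2%.
- f = 0.40, N = 63 with no attrition: 10.08, power 79.8%.
- f = 0.40, N = 66, the smallest total in equal arms that reaches 80%: 10.56, power 81.8%.
- f = d/2 = 0.424, N = 57: power 80.2%.

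So 57 is reproduced only with f = d/2, which is the two-group conversion. With three arms and a largest difference of 0.85 SD, f = 0.85 × √2/3 = 0.401 if G1 equals one of the other arms, and 0.85/√6 = 0.347 if G1 is midway. In the midway case 57 women give 62%.

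**2. Power of the deciding contrasts.** For one contrast, the noncentral t has df 3n − 3 and noncentrality d√(n/2).
- n = 19: 0.848 × √9.5 = 2.61, critical value 2.306 at 0.025.
- n = 21: 0.848 × √10.5 = 2.75, critical value 2.299 at 0.025.

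Full Holm was simulated with the shared G2 arm. G2–G0 is rejected if its p < 0.025, or if its p < 0.05 and the p for G2–G1 is < 0.025.

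| Evaluable per arm | G2–G0 at 0.025 | G2–G0 at 0.05 | G2–G0, full Holm (G1 midway / G1 = G0) | G2–G1, full Holm (G1 midway / G1 = G0) |
|---|---|---|---|---|
| 19 | 62% | 73% | 63% / 68% | 23% / 68% |
| 21 | 67% | 77% | 68% / 73% | 26% / 73% |

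The position of G1 is an assumption, because the plan states no separate effect for G2–G1. For scale, 80% at 0.025 with this d needs 28 evaluable women per arm.

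**3. What 3.48 measures.** With two time points, a random intercept and complete data, the Group × Time contrast is in essence a comparison of change scores. If 3.48 is already the SD of change, the mixed model therefore adds no power. If 3.48 is the SD of scores, the SD of change is 3.48 × √(2(1 − ρ)). At 0.025 with 19 per arm and assumed ρ:
- ρ = 0.5: SD 3.48, power 62%.
- ρ = 0.6: SD 3.11, power 73%.
- ρ = 0.7: SD 2.70, power 85%.

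**4. Sensitivity of the effect (all assumed; 19 per arm, alpha 0.025).**
- G0 gains 0.5 point: d = 2.45/3.48 = 0.704, power 45%. Gains 1.0: d = 0.560, power 29%.
- G0 declines 0.5 point: d = 3.45/3.48 = 0.991, power 77%. Declines 1.0: d = 1.135, power 88%.
- 30% of G2 gain nothing: d = 0.7 × 0.848 = 0.593, power 32% (36% with 21 per arm).

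**5. Success rule.** With d = 0.85, 19 per arm and G1 = G0, Holm rejects at least one contrast in 77.8% of runs and G2–G0 in 68.1%. G2–G1 alone is therefore significant in 77.8 − 68.1 = 9.7%. With G1 midway it is 64.3 − 63.3 = 1.0%. Section 3.9 treats such a result as a significant primary comparison. Section 3.1 labels it a secondary one.

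**The case against.** The best defence concerns 3.48. Section 2.4 calls it only a common SD. If it is the SD of scores and the T0–T1 correlation is about 0.7, G2–G0 has more than 80% at 0.025, and the word conservative, which there compares ANOVA with a repeated-measures model, can be defended. Section 3.2 quotes a test–retest r of 0.92, although that need not hold over four months of treatment. This stands as far as it goes: a reader might infer that the word is simply false, and the document does not establish that. But Section 2.4 ties the calculation to change and states no correlation, so the claim is unsupported as written.

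Other stronger readings also fail:
- **That the trial at least powers the omnibus test.** It does not at the stated f.
- **That control-arm gain pushes power far lower.** Section 2.6.1 describes G0 as following the natural course under treatment, so decline is equally possible and would raise power. Nor can the document show whether the 2.95 was net of a control. It states no control-arm change.
- **That 30% of G2 gaining nothing is the expected case.** A woman below the 22-of-32 threshold may have attended 21 sessions. The figure is an illustration.
- **That Holm is an error.** It validly controls family-wise error, and it tests G2–G0 at 0.05 once G2–G1 is rejected.

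Section 6 admits that attrition may cost power. That does not cover the mismatch between the sized test and the deciding tests.

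**Conclusion.** The point holds. The document gives 80% power for a test that does not decide the trial, and that figure does not follow from its stated f. Taking 3.48 as the SD of change, G2–G0 falls short of 80% in every case in the table, including an unadjusted 0.05 with no attrition (77%). G2–G1 power depends almost wholly on how G1 performs, about which the plan says nothing.

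The contrast figures rest on that reading of 3.48 and on 2.95 being the true difference from G0. The f/N mismatch rests on neither.

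The fully-powered claim is wrong on any reading: intention-to-treat keeps the numbers, but non-adherence dilutes the effect. The ranking of G2–G1 is a conflict of labels. Section 3.1 states no decision rule, so the document does not formally give two opposite verdicts, but it leaves the success rule open to dispute.

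**What to change.** No change in N is asked for.

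- **Section 2.4.** State the power for G2–G0 and for G2–G1 under the testing rule actually used, with labelled ranges for control-arm change in both directions and for non-adherence. Correct the f/N mismatch. Say whether 3.48 is the SD of change or of scores. Drop the word conservative unless a stated T0–T1 correlation supports it.
- **Section 3.9.** Delete the claim that the analysis stays fully powered under non-adherence.
- **Sections 1, 3.1 and 3.9.** Give G2–G1 one status and state one success rule.

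One rule that fits the ranking in Sections 1 and 3.1 is to test G2–G0 at 0.05 and, only if it is significant, G2–G1 at 0.05. With 19 per arm this gives G2–G0 73%. It is a choice for the sponsor. It gives up a confirmatory G2–G1 claim if G2–G0 fails, lowers G2–G1 power from 68% to 59–60% if G1 = G0, and still does not reach 80%. Keeping Holm is equally valid if both contrasts are called primary throughout.

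The cost is wording in four sections and a lower stated power. The rule should be settled before outcome data are seen by arm.

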### 2.5. Randomization and Allocation Concealment

To ensure numerical balance and a homogeneous distribution of prognostic factors across the three study arms, a stratified block randomization method will be employed. Randomization will be stratified based on two baseline prognostic variables: (1) baseline cognitive status, categorized according to the Montreal Cognitive Assessment score (MoCA < 26 vs. ≥26), and (2) oncological treatment modality, classified according to its systemic neurotoxic potential: systemic chemotherapy with or without radiotherapy versus endocrine/hormone therapy or localized radiotherapy alone.

Following stratification, participants will be randomly assigned to one of the three study arms using randomly varied blocks of size 3 and 6. The random allocation sequence will be generated before the start of recruitment by an independent researcher using Epidat 4.2 software. This researcher will not be involved in participant recruitment, eligibility assessment, baseline or post-intervention outcome assessment, intervention delivery, data management, or statistical analysis.

The random allocation sequence will be stored in a password-protected file and will remain inaccessible to the Principal Investigator, oncology team, intervention providers, outcome assessors, and statistician until eligibility has been confirmed, written informed consent has been obtained, and all baseline assessment procedures (T0) have been completed.

After completion of T0, the Principal Investigator will access the next available allocation within the corresponding stratified stratum and assign the participant to the allocated study arm. The assigned group will then be communicated to the intervention coordinator. The allocation will be recorded in a secure allocation log maintained separately from the assessment database.

This procedure will ensure that group allocation cannot influence eligibility confirmation, informed consent, or baseline assessment. Because the Principal Investigator will become aware of group allocation after T0, this trial will be conducted as an open-label study, and this limitation will be addressed through standardized assessment procedures and blinded statistical analysis using neutral group labels.

The three study arms are defined as follows:G0 (Control Group): Health Education Programme.G1 (Active Comparison): Cognitive Training (CT).G2 (Experimental Group): ALMA.

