## Abstract

**Background**: Cancer-related cognitive impairment is a frequent and clinically relevant concern among women with breast cancer, particularly during active oncological treatment, with potential consequences for memory, attention, executive functioning, daily autonomy, emotional well-being, and quality of life. This study aims to evaluate the effectiveness of the Playful Attention and Active Memory intervention (ALMA) on cognitive functioning in women with breast cancer undergoing active oncological treatment. **Methods**: This single-centre, three-arm, parallel-group randomized controlled trial at the University Healthcare Complex of Salamanca (Spain) will evaluate 63 women with breast cancer undergoing active oncological treatment. Participants will be randomized (1:1:1) into a health education control group, an individual non-tailored cognitive training group, or the ALMA multidimensional group intervention (two 120 min face-to-face sessions/week for four months, combining psychoeducation, targeted cognitive stimulation, and group feedback). Assessments will occur at baseline and post-intervention. The primary outcome is objective global cognitive performance (Montreal Cognitive Assessment). Secondary outcomes include perceived cognitive function, everyday cognition, functional autonomy, anxiety, sleep quality, performance status, and everyday memory failures. Intention-to-treat analysis using linear mixed models will perform prespecified comparisons of ALMA versus both other groups. **Expected results**: This study is designed to provide evidence on the potential value of a structured, multidimensional cognitive intervention delivered during active breast cancer treatment. By comparing ALMA with both health education and individual cognitive training, the trial may clarify whether the integration of psychoeducation, ecological cognitive stimulation, and group-based support offers additional benefits beyond cognitive practice alone. The inclusion of objective, subjective, and functionally oriented outcomes strengthens the clinical relevance of the protocol and may contribute to the development of more comprehensive supportive care strategies for cancer-related cognitive impairment. Trial registration: This protocol is registered at ClinicalTrials.gov under the identifier NCT07165912.

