### 2.11. Administrative and Oversight Information

This manuscript describes version 1.0 of the ALMA trial protocol, dated June 2026. The trial is registered at ClinicalTrials.gov under the identifier NCT07165912. The trial registry record will be kept consistent with the final approved protocol, including the study design, target sample size, intervention arms, eligibility criteria, outcome measures, and assessment time points.

The Principal Investigator will be responsible for the overall coordination of the trial, protocol implementation, supervision of recruitment, safety reporting, data integrity, and communication with the Research Ethics Committee. The oncology team will identify potentially eligible participants during routine clinical care. The principal researcher will obtain informed consent, administer baseline and post-intervention assessments, maintain study documentation, and monitor adherence. The principal researcher will be responsible for the intervention and deliver the ALMA sessions according to the intervention manual and will document attendance, adverse events, and protocol deviations.

There is no external or commercial sponsor for this study. The University of Salamanca will provide institutional oversight in accordance with applicable ethical, legal, and institutional requirements.

Given the low-risk, non-pharmacological nature of the ALMA intervention and the individual cognitive training programme, no independent Data Monitoring Committee will be established. The Principal Investigator and authorized members of the research team will conduct trial monitoring internally. Monitoring activities will include periodic review of recruitment progress, eligibility documentation, informed consent forms, adherence records, intervention attendance logs, adverse event reports, protocol deviations, withdrawal reasons, and completeness of outcome assessments.

No routine external auditing is planned. However, essential study documents may be reviewed by the University of Salamanca, the Research Ethics Committee, or other competent institutional authorities if required. Documents available for review may include the approved protocol and amendments, ethics approval documentation, informed consent forms, screening and enrolment logs, randomization and allocation records, adverse event logs, protocol deviation records, data management logs, and pseudonymized datasets.

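### The Principal Investigator opens the allocation sequence for each participant, so the absolute guarantee in Section 2.5 that allocation cannot influence eligibility, consent or baseline assessment is not supported

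*Protocol article*

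**What the plan says.** Section 2.5 of the protocol article has an independent researcher generate the sequence before recruitment starts. The sequence is kept in a password-protected file, closed to the Principal Investigator and others until eligibility, consent and T0 are complete. Then: "After completion of T0, the Principal Investigator will access the next available allocation within the corresponding stratified stratum and assign the participant". The section concludes: "This procedure will ensure that group allocation cannot influence eligibility confirmation, informed consent, or baseline assessment". It also says that the Principal Investigator learns each allocation after T0 and that the trial is therefore open-label.

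Allocation is 1:1:1 to three arms, "using randomly varied blocks of size 3 and 6", within four strata formed by treatment modality and by baseline cognition, "categorized according to the Montreal Cognitive Assessment score (MoCA < 26 vs. ≥26").

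On roles, Section 2.11 states: "The principal researcher will obtain informed consent, administer baseline and post-intervention assessments, maintain study documentation, and monitor adherence". It gives delivery of the ALMA sessions to the same principal researcher. Section 6 confirms that the professional who does the initial and final assessments also runs the ALMA groups.

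The article names no separate password holder, no release by a third party and no row-by-row masking. The independent researcher's only stated task is to generate the list.

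**The concern.** Concealment has to hold for the next participant as well as for the one whose T0 has just been completed. The person who opens the file after one woman's T0 goes on to recruit the next woman, and by then knows at least all past allocations in each stratum and the published block lengths. If the file displays more than one row, that person knows much more.

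That knowledge could affect when consent is sought, how a borderline eligibility question is settled, and how a MoCA near 25 or 26 is scored. The last matters twice. The T0 MoCA chooses the stratum list from which the allocation is drawn, and it is also the baseline of the primary endpoint, the T1 minus T0 change (Section 3.2).

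The listed countermeasures do not reach this. The scripts, neutral posture and timers in Section 6 are aimed at T1 expectancy effects, and the blinded statistician in Section 3.5 works after any tilt is already in the data. The limitations admit unblinded assessment but not weakened concealment.

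**Working it through.** The article gives no figure on concealment, so there is none to reproduce. Predictability can be computed from the stated design.

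**Inputs from the article.** Three arms, 1:1:1 (Abstract). Blocks of 3 and 6, and 2 × 2 = 4 strata (Section 2.5). 63 women (Section 2.4), so 63/4 ≈ 16 per stratum if equal.

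**Assumptions, not stated in the article.** Blocks of 3 and 6 equally likely. Stratum sizes 16/16/16/15, with 30/15/12/6 as a range check. The observer knows the block lengths and all earlier allocations in the stratum, but not the length of the current block.

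**Case 1: opening the file shows the list.** Every allocation after the first opening is known. No calculation is needed.

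**Case 2: one row is seen at a time** (the case most favourable to the plan).

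- First in a stratum: 1/3 for each arm.
- Second in a stratum: the arm just used has probability 0 in a block of 3 and 1/5 in a block of 6. So 0.5 × 0 + 0.5 × 1/5 = 0.10, which leaves 0.45 for each other arm.
- Third, if the first two differ: the probability of differing is 1 in a block of 3 and 4/5 in a block of 6, so the block is a 3 with probability 0.5/(0.5 + 0.4) = 5/9. The remaining arm has probability 5/9 × 1 + 4/9 × 1/2 = 7/9 ≈ 0.78.
- Third, if the first two are the same: the block must be a 6, that arm is used up, and the others have 0.5 each.
- The best guess at the third place is therefore right with probability 0.9 × 7/9 + 0.1 × 0.5 = 0.75. Simulation gave 0.752.

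Carrying the same updating through 2,500 simulated sequences gives:

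| | 16/16/16/15 | 30/15/12/6 | By chance |
|---|---|---|---|
| Best guess correct | 56% | 57% | 33% |
| Out of 63 | about 35 | about 36 | 21 |
| Allocation certain | 7.2% (about 5 women) | 7.7% (about 5 women) | 0 |
| At least one arm ruled out | 19.3% (about 12 women) | 19.7% (about 12 women) | 0 |

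No allocation is certain before the fifth place in a stratum.

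**Sensitivity.** A cruder rule, guessing the arm with the fewest allocations so far in the stratum (ties at random), was run with block mixes from 30/70 to 70/30 and strata as uneven as 40/13/7/3. It was right 55–58% of the time.

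**What the fix would change.** With the same crude rule and other block sets, for equal and unequal strata: 3/6/9 gives 53% and 54%, 6/9 gives 52% and 52%, fixed 9 gives 50% and 50%. The rule uses only past allocations and needs no knowledge of block lengths.

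**The case against.** Four points on the other side deserve weight.

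**Access to the next allocation can be read as access to one row.** A reader might infer that concealment is lost for everyone from the second participant on. The text does not support that. It holds only if the file displays later rows, which Section 2.5 neither states nor excludes, and an article may leave release mechanics to the full protocol. Under single-row release, a second participant in a different stratum is still at 1/3 per arm, and the loss is partial predictability.

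**The titles differ.** Section 2.5 lists the Principal Investigator apart from intervention providers and outcome assessors, and Section 2.11 gives consent, assessment and delivery to the principal researcher. That they are one person is an inference. It is a strong one, because Section 2.5 answers the Principal Investigator's awareness of allocation with standardized assessment procedures, which makes sense only if that person assesses.

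**The 56–57% is a property of permuted blocks in an unmasked single-centre trial.** It does not measure who opens the file. Whoever delivers ALMA learns the arms in any case. This stands, and it limits what the fix can claim.

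**Opportunities for selection are narrower than they might seem.** The oncology team identifies women consecutively, a screening log records exclusions and refusals, and eligibility is broad (Sections 2.2 and 2.3). These limit who is referred. They do not govern the consent conversation, the final eligibility decision or the scoring of T0.

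Unblinded T1 scoring is a separate matter that the article already admits, and it adds no weight here.

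**Conclusion.** The guarantee in Section 2.5 is stated as absolute, and the procedure described cannot deliver it. This is a statement in the article that its own procedure does not support, rather than a detail left to another document.

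The size depends on a fact that the article leaves open. If the opened file shows the list, all allocations after the first opening are known. If rows are released singly, the best guess is right about 56–57% of the time against 33%, from the second participant in each stratum on, with about 7–8% of allocations certain. These figures rest on equal block-size probabilities and strata between 16/16/16/15 and 30/15/12/6. The weight given to role overlap rests on the inference that the Principal Investigator and the principal researcher are the same person.

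Nothing here shows that selection will occur. The plan leaves an avoidable route open and then states that it is closed.

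**What to change.** Change Section 2.5 in two places.

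1. **Release.** The independent researcher who generated the sequence holds the file and the password. That researcher releases one time-stamped assignment at a time, only after eligibility, consent and T0 data have been entered and locked. The Principal Investigator never has access to the sequence. A randomization module would serve equally well if the chosen data-capture platform has one. Section 3.7.1 names REDCap or an equivalent for data capture only, so a reader should not infer that such a module is already planned.
2. **Wording.** Replace the absolute guarantee with a statement that the next assignment is concealed until T0 is locked, and that some predictability remains because the trial is open-label with stratified permuted blocks.

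The cost is a small added task for the independent researcher, whose stated role now ends with generating the list, and a short wait at each release.

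The first change removes the risk of seeing the list ahead. It does not lower the guess rate. Larger block sets would bring that rate down only to about 50–54%. With three arms at 1:1:1 they must be multiples of 3, and in strata of about 16 they would cost some balance. Withholding the block lengths would not stop the fewest-so-far guess. Neither is a substitute for the first change.
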